#### Intervention Delivery

As described earlier, in our previous work, we developed a stress assay that used self-reported survey data on different stress response indicators (ie, negative affect, perseverative cognitions, and subjective stress) and several stress targets (ie, RRPs) to be able to derive person-specific means and SDs [4,5]. Using this information, we were able to establish person-specific thresholds that would indicate meaningful derivations from an individual’s norm (ie, identifying when they are stressed), as well as moments or days that were associated with poor health behavior enactment (eg, sleep and physical activity [9,10]). In this study, we aim to use this assay to identify “moments of risk” and intervene “just in time” to prevent downstream impacts on our health behaviors of interest (ie, sleep and physical activity). To provide intervention content at these moments of elevated stress while also maximizing the probability of participant engagement with the intervention content, we developed several pragmatic principles and boundaries to guide our intervention delivery. We refer to these general principles and rules as our intervention algorithms. These algorithms, when paired with the smartphone survey data in real time (ie, uploaded from the smartphone to the study server via mobile data plan), allow us to process the participant’s survey data, aggregate the information across moments and days, provide a solution (ie, trigger) for whether or not intervention content should be delivered to the participant at that moment, and subsequently deliver the content to the participant, all in near real time.

To provide us with the greatest opportunity to interfere with current or ongoing stress responses and to maximize the probability of availability, we decided that interventions would only be delivered immediately following the completion of a survey (beeped or evening). This ensures that the participant is near their study smartphone should an intervention be delivered. It also allows us to intervene in active or ongoing stress responses in the contexts in which they occur. Although this approach has some limitations, such as requiring the individual to have the mental resources to engage with the intervention during periods of elevated stress, it was chosen in an attempt to optimize intervention impact and participant engagement. This approach also provides a natural connection between this study’s intervention and survey types.

We have created 2 overlapping intervention algorithms to match intervention types (ie, microinterventions and end-of-day intervention) to survey data (ie, beeped and evening) while accounting for participant availability and burden. We developed the JIT intervention algorithm (Figure 2) to process information from the beeped surveys and trigger brief microinterventions during the day. Then, we developed the end-of-day intervention algorithm (Figure 3) to process information from the evening survey and trigger the longer end-of-day intervention. These algorithms, when combined, allow us to leverage our stress assay to detect moments of elevated stress responses in individuals at both the moment and day level, providing brief interventions in the moment or longer and more focused interventions at the end of the day, when there are generally fewer daily demands on an individual.

In broad terms, the intervention algorithms use survey data from phase 1 to derive person-specific thresholds for each participant to inform intervention delivery in phase 2. This approach highlights the importance of selecting highly adherent participants to continue to phase 2 of the study. Once enrolled in phase 2, person-specific thresholds will be continuously updated as surveys are completed and intervention content is delivered. When survey data are collected from participants throughout the day and in the evening, it will be automatically uploaded and processed in the algorithm in real time to determine whether a participant’s state indicates elevated stress levels. The algorithm will access all previous responses preceding that specific moment and the person-specific thresholds to do this. This information will then be combined with the current survey data to determine whether there is a meaningful deviation from an individual’s norm. Each meaningful score will be weighted and combined with other meaningful scores for that specific moment to derive a weighted summary risk score. Each moment’s risk level will then be evaluated based on the weighted summary risk score. Depending on this score, an intervention may be delivered to a participant at that moment, and, in some cases, a longer intervention may also be scheduled for delivery at the end of the day. This process will be repeated continuously for each participant as survey data are uploaded.

As an initial attempt to manage participant expectations and burden in this study, we incorporated a set of rules that will govern the upper and lower limits of intervention delivery (ie, ensure both a minimum and maximum frequency) and serve 2 purposes. First, our lower bound rules ensure that at least some intervention material is pushed out to each participant who is randomized into the JIT intervention condition, even in the absence of person-specific elevated stress. This includes providing a microintervention at least every 48 hours, regardless of whether elevated stress levels triggered an intervention, and an end-of-day intervention at least once every 5 days. We think this approach will keep participants engaged while providing a minimum “dose” of intervention content. We are also aware that participants in this study may experience stress below our intervention threshold (especially as their time and exposure to intervention content progresses) or that we may miss some stress responses or events with our survey schedule. Therefore, providing some minimum level of intervention content could provide the skills or resources to maintain the treatment effect, prevent future stress responses, or buffer any ongoing subthreshold stress. Second, the upper bounds of our intervention delivery will prevent us from overwhelming participants should they experience a bout of frequent or intense stress. To prevent undue participation burden related to engaging in microintervention content, we will limit microinterventions to a maximum of 3 on any given day (between 8 AM and 9 PM). We will provide the option to dismiss or delay any intervention for up to 20 minutes. We will have access to the uptake of all intervention content, including the date and time it was delivered and initiated by the participant, its duration, and the completion time.

#### Active Control Condition (Self-Monitoring and Stress Management Education)

In this study, participants enrolled in the active control condition will engage in self-monitoring for the duration of phase 2. Although there is some evidence that self-monitoring on its own might be a strategy for reducing negative affect and perseverative cognition [41], we wanted to provide a more stringent test of the “just in time” aspect of our stress management intervention. Therefore, we decided to bolster our comparison condition by providing access to a stress management education module comparable to any usual care stress management resource that an individual could access if needed. With this in mind, we developed 8 brief readings and tips that focused on stress education and the impact of stress in everyday life and adapted these materials into a web-based reading or reference module [40]. All participants enrolled in phase 2 of the study will have access to this module on the home screen of their study smartphone. If the module link is activated, they will be provided with a summary of the purpose of the module, followed by a list of 8 topics they can choose. Each module will take about 2 minutes to read and is followed by a brief, generic stress management tip that can be incorporated into everyday life. The stress management tips were derived from the same 4 categories outlined earlier, with 2 activities from each of the 4 categories included in the module. Participants will have access to this module 24 hours per day for the entirety of phase 2 and can access the readings as often as they want. User statistics will be collected each time a participant accesses the module, including the topics accessed, the number of times the module is accessed per day across the study, and a singular item about acceptability.

#### Proposed Analyses and Analytical Approach

All collected data will be subjected to a rigorous data-cleaning procedure to identify invalid data points (eg, out-of-range, implausible, and outlier variables will be scrutinized). General descriptive statistics (ie, mean, median, percentages, and SD) will be used to characterize the study sample. To evaluate the effect of the smartphone-delivered JIT intervention on RRP (specific aim 1), we will use mixed-effects models to evaluate any significant differences in RRP scores between the 2 study groups (ie, intervention group vs control group). In addition to the main effect differences between the 2 groups, we are interested in the potential cumulative effect of receiving multiple interventions across the 2-week study duration (testing a “dose” effect of the microinterventions) or whether potential benefits do not occur immediately but rather develop during the intervention period (eg, if it takes some time for the JIT intervention to lower stress responses). To evaluate this latter effect, we will test the group-by-time interaction effect in a multilevel (eg, momentary RRP nested within days, days nested within person, and person nested in group) mixed effect model. Analyses will be conducted using the SAS statistical program (version 9.4; SAS Institute Inc).

For our second aim, evaluating whether the intervention is associated with improved health behavior levels (ie, sleep and physical activity), we will use the same approach described for our first aim. That is, we will evaluate the overall treatment effect and how this effect changes with time. Unique in this evaluation, we will test these relationships using continuous outcome (ie, the amount of time spent on these health behaviors) as well as the likelihood of meeting the threshold for recommended levels of physical activity (≥150 minutes of moderate to vigorous physical activity/week) and sleep (>7 hours/night). That is, we are interested in finding out whether participants who receive the innovative JIT intervention were more likely to meet recommended levels of physical activity or sleep.

Finally, we will test whether changes in RRPs mediate the group-level effects of the intervention on health behaviors. In other words, we want to evaluate whether any benefits observed in health behaviors are due to the changes in stress responses (RRPs). All evaluations will be conducted using an intent-to-treat analysis, with imputation conducted for missing data as appropriate, and a per-protocol (completers) analysis. Given the large number of analyses planned, we will evaluate and implement appropriate methods to reduce the likelihood of false positives (eg, false discovery corrections). Theoretically informed but more exploratory analyses will be conducted to examine if there are individual difference moderators of observed effects.

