### Ethical Considerations

The Pennsylvania State University Institutional Review Board approved all study procedures (STUDY00012740). All participants provided informed consent. All study data are deidentified and encrypted. Participants were compensated equitably for participation according to what study phases and components they completed, as detailed in the Procedures section.

### Phase 1

Phase 1 of this study serves 3 primary purposes. First, it is a data-capture period that enables us to collect individual baseline data on each participant to be used to inform the JIT intervention algorithm in phase 2. Second, it allows us to screen for participant compliance with the protocol and ensure that those enrolled in phase 2 meet minimum standards for data completeness (ie, >70%). Third, this period allows us to exclude participants who do not regularly report stress during everyday life and thus may not be impacted by our intervention.

### Phase 2

Phase 2 is the clinical trial portion of the study and will serve as the between-group test of our JIT intervention on night sleep and physical activity. This study phase will be initiated immediately following phase 1 and is 3 weeks long. Participants who are eligible for phase 2 will be randomized into one of two conditions as follows: (1) JIT intervention (ie, JIT stress management, self-monitoring, and web-based stress education module) or (2) active control (ie, self-monitoring and web-based stress education module). The first 2 weeks of phase 2 are the active intervention period, while the final week is a self-monitoring period.

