### Randomization

Randomization for this study will occur upon enrollment into phase 2 using discrete codes entered into the smartphone app by a research assistant blind to study goals. Participants will be allocated on a 2:1 ratio that favors the JIT intervention condition to provide a sample size large enough to support our planned analyses. To balance participant characteristics within the study conditions, participants will be equally randomized across 3 age categories (including those aged 35 to 44, 45 to 54, and 55 to 65 years) and by sex (male and female). Masking of the participant group identities from the training personnel, data collectors, and analysts will be used. Group assignments will be unmasked for analysis when the trial is complete and after all data have been entered.

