### Sample Size

Our initial power calculations suggest that our study target for participants enrolled in phase 2 should be 210 (n=140, 66.7% assigned to the JIT intervention condition and n=70, 33.3% assigned to the active control condition). In our previous work with a similar assessment schedule, we observed compliance rates of >70% on the momentary surveys and >80% on the device wear time across 2 weeks in 95.2% (120/126) of the participants (unpublished data). Of those participants, the lowest quartile reported approximately 3 stressor events across 2 weeks. Thus, we estimate that approximately 15% of participants enrolled in phase 1 will not qualify for phase 2 due to no reported stressors or low compliance rates with study procedures. It is also likely that some participants may choose not to continue participation in phase 2 even if they are eligible due to the intensive assessment schedule. We estimate that refusal will account for 25%, and an additional 10% of those participants may either drop out during phase 1 or become ineligible. Thus, we estimate that up to 50% of the participants enrolled in phase 1 may not continue to phase 2. Therefore, we expect to recruit and enroll approximately 450 participants in phase 1 to reach our target of 210 participants in phase 2.

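### The Aim 1 and Aim 2 models as described name neither the phase 1 outcome level nor the randomisation factors; followed as written, they give up precision on the continuous outcomes

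*Protocol article*

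**What the plan says.** Proposed Analyses and Analytical Approach describes the Aim 1 model: "we will use mixed-effects models to evaluate any significant differences in RRP scores between the 2 study groups". It adds a group-by-time interaction in a multilevel model, with moments within days within persons as the example of nesting. The time spans it mentions are the two study weeks and the intervention period. For Aim 2 it states "we will use the same approach described for our first aim", applied both to continuous amounts and to meeting recommended thresholds for activity and sleep. No covariate is named for either aim.

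Randomization states that "participants will be equally randomized across 3 age categories" and also by sex. The Phase 1 subsection gives three main purposes for the run-in week. The first is to "collect individual baseline data on each participant to be used to inform the JIT intervention algorithm in phase 2"; the others are to screen for compliance and to exclude people who do not regularly report stress. Adjusting the outcome models is not among them. Procedures shows that phase 1 uses the same eight daily surveys and the same two devices as phase 2.

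Eligibility for Phase 2 requires survey compliance above 70%, at least one reported stressor and at least 5 valid nights. It says that phase 1 activity data are not checked for completeness at that point.

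**The concern.** Stress, sleep and activity can be expected to differ between people in ways that persist from week to week. If the participant's own earlier level is not in the model, that stable variation stays in the standard error of the group difference, and a chance imbalance between 140 and 70 people goes uncorrected. Factors balanced at randomisation and then left out of the model make the standard error conservative to the extent that they are prognostic.

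Enrolment is reported complete at 213, so adjustment is one of the few remaining ways to gain precision. Timing also matters. Results says that analyses have not begun, and Randomization says that groups are unmasked once all data are entered. Covariates fixed before that moment are credible; covariates chosen afterwards invite selection, particularly as the article itself expects a large number of analyses.

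**Working it through.** **Inputs from the article.** Sample Size: "Our initial power calculations suggest that our study target for participants enrolled in phase 2 should be 210", split 140 and 70. Check: 210 × 2/3 = 140 and 210 × 1/3 = 70. The 210 itself cannot be reproduced, because the article gives no alpha, power, effect size or SD.

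**Assumptions.** Two-sided alpha 0.05, 80% power, effects in SD units of a person-level mean, and a phase 1 to phase 2 correlation r from 0.1 to 0.8.

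**Unadjusted.** Variance factor = 1/140 + 1/70 = 0.02143, square root 0.1464. Detectable difference = (1.960 + 0.842) × 0.1464 = 0.410 SD. The same 0.1464 SD is the standard error of a chance difference between arms at baseline.

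**Adjusted for baseline.** For a continuous outcome the standard error is multiplied by √(1 − r²). The equivalent unadjusted sample is 210 / (1 − r²).

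| r (assumed) | SE factor | Detectable difference (SD) | Power at 0.30 SD | Equivalent unadjusted N |
|---|---|---|---|---|
| none | 1.000 | 0.410 | 53.6% | 210 |
| 0.1 | 0.995 | 0.408 | 54.0% | 212 |
| 0.3 | 0.954 | 0.391 | 57.5% | 231 |
| 0.5 | 0.866 | 0.355 | 65.8% | 280 |
| 0.7 | 0.714 | 0.293 | 81.9% | 412 |
| 0.8 | 0.600 | 0.246 | 92.7% | 583 |

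**Which r is plausible.** Take the outcome as a 14-day mean and the baseline as an m-day mean, with day-level intraclass correlation ICC and a person level that does not drift. Then r = ICC / √[(ICC + (1 − ICC)/m)(ICC + (1 − ICC)/14)]. For an assumed ICC of 0.2 to 0.6:
- m = 5 to 7 gives r = 0.66 to 0.93. Entry requires at least 5 valid nights, so sleep fits this case.
- m = 1 gives r = 0.39 to 0.76. This is nearer to a stress score resting on one reported stressor.

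**Age band and sex alone.** The SE factor is √(1 − R²): 0.990, 0.975 and 0.949 for an assumed R² of 0.02, 0.05 and 0.10. Power at 0.410 SD moves from 80.0% to 80.8%, 82.0% and 84.0%. The baseline outcome is therefore the substantive part.

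**Scope.** The figures concern the average group difference on continuous outcomes. The group-by-time test already contrasts each person with himself or herself over time and has less to gain from the baseline level. The √(1 − r²) factor does not apply to the odds ratios for the threshold outcomes.

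**The case against.** The strongest objection is that the article is silent rather than decided. It does not say that the models are unadjusted or that phase 1 records are left out, and a condensed article commonly leaves the covariate list to a full plan that is not shown here. This stands as far as it goes: a reader might infer that the sponsor has chosen to discard the baseline, and the text does not support that. The three purposes given for phase 1 are called primary, not exclusive, and the mediation aim refers to changes in the stress scores, which presupposes some reference level. The point survives because the model is otherwise set out concretely (contrast, interaction, time span, nesting), and a better model is available from data the trial already collects.

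Three further objections also stand and limit the claim:
- **A usable baseline may not exist for everyone.** Activity data are not checked before randomisation, and one stressor is enough to enter phase 2, so a baseline recovery or pileup score may be very thin.
- **Stress scores may already be person-referenced.** Intervention Delivery describes deviations from an individual's norm, with thresholds first set from phase 1. If the outcomes are scored that way, much of the stable level is already removed and r could be low.
- **Precision is not lost on every outcome.** In a logistic model, covariates change the estimand to a conditional odds ratio, and the standard error of the log odds ratio does not shrink, although power may rise.

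**Conclusion.** The point holds in a limited form. Followed as written, the Aim 1 and Aim 2 models give a valid comparison that is less precise than it need be for the continuous outcomes. The detectable difference is 0.41 SD unadjusted; adjusted, it ranges from 0.41 SD (r = 0.1) to 0.25 SD (r = 0.8). These figures rest on assumed alpha, power and correlation, none of which the article states. A material gain is most likely for sleep, plausible for activity where phase 1 data are adequate, and uncertain for sparse or person-referenced stress scores. Age band and sex alone would cut the standard error by about 1% to 5% under the assumed R².

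Two stronger inferences should be avoided. The unadjusted analysis is not biased or invalid, because randomisation protects it. Nor does the article show that baseline data are held on every participant and deliberately ignored. This is an improvement worth making before unmasking, held with moderate confidence because a fuller plan may already contain it.

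**What to change.** Before unmasking, state that the primary Aim 1 and Aim 2 models adjust for the phase 1 value of the same outcome and for age band and sex. If the full plan already does so, confirming that is enough.

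- **Complete phase 1 data:** enter the phase 1 person mean as a covariate, with fixed effects for age band and sex.
- **Phase 1 data that may be incomplete, notably activity:** enter phase 1 days as responses, with the arms constrained to a common mean before randomisation, so that nobody with phase 2 data is dropped. Give each person separate but correlated effects for phase 1 and phase 2, so that the data determine how much weight the baseline gets.
- **Threshold outcomes:** state that the adjusted odds ratio is conditional, or report a standardised risk difference.

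The unadjusted model can be kept as a sensitivity analysis. The cost is model wording and some programming; no new data, visits or participants are needed.

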### Participants

To examine the impact of our intervention on our primary outcomes without the influence of age-related stressors or increased probability of health comorbidities that could impact our measures of sleep and physical activity, our target population will be generally healthy middle-aged adults. Specifically, we will recruit English-speaking men and women aged 35 to 65 years who report good general health and are free of physical limitations from the mid-Atlantic region of the United States.

We will exclude people who report (1) residing in the same household as current or former participants (to prevent any contamination of the intervention or unblinding of condition allocation); (2) an inability to answer smartphone survey SMS text messages due to restrictions or policies in the workplace; (3) a diagnosis of a mental health condition that required a medication adjustment or hospitalization within the last 3 months; (4) being a primary caretaker for a parent, child, and family member who is severely disabled; (5) employment that requires shift work as this will result in abnormal sleep patterns; (6) a diagnosis of sleep apnea, use of a continuous positive airway pressure machine, or score above threshold on STOP-BANG; (7) the use of physician-prescribed pharmaceutical sleep aids or over-the-counter sleep aids for ≥3 days per week; (8) an inability to be physically active or who have medical contradictions for physical activity; or (9) physical exercise of ≥200 minutes per week at a moderate or vigorous intensity or ≥10 hours of walking per week as this raises the possibility of ceiling effects on activity.

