Survey data from phase 1 of the study will be used to inform the delivery of the JIT intervention in phase 2. Therefore, it is essential for participants who enter phase 2 to meet the minimum criteria for complete data on which to apply our intervention rules. For this reason, we will assess participant compliance with the study procedures and data completeness before inviting participants into phase 2. Specifically, participants who complete phase 1 will be eligible for phase 2 if they (1) return all study devices, (2) report at least 1 stressor in their surveys during the 1-week run-in period, (3) meet an acceptable rating threshold for survey compliance (ie, >70%), and (4) have valid accelerometry data for at least 5 nights during the 1-week study period. Given that these compliance checks will be conducted during a brief session, the physical activity data will not be assessed for completeness as it requires considerable time to download and review.

Once all devices are obtained and compliance checks are done, participants will be compensated according to completed study procedures. At the time of compensation, each participant will either be dismissed or invited to participate in phase 2 of the study. Those deemed eligible to participate in phase 2 will receive a brief overview of study procedures. They will participate in the consent procedure for phase 2 and a refresher training session if interested. If they are not interested, they will be dismissed.

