#### Objective Physical Activity

The physical activity data will be aggregated into 1-minute epochs. Using the sleep and wake times from the sleep data, all sleep periods will be excluded in the subsequent data aggregation process. Furthermore, any continuous sitting or standing events that are >5 consecutive hours will be classified as nonwear and will also be excluded. The remaining valid wake period will be classified into either time spent sedentary, standing, or stepping. Time spent stepping will further be classified into time spent in light physical activity or moderate to vigorous physical activity using the 100 steps per minute cut point [37]. Other relevant objective physical activity outcome variables will include step count and number of sit-to-stand transitions. The physical activity data will be further aggregated depending on the level of analysis as necessary (eg, hourly, daily, and person-level summary).

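### Entrants may already meet the 150 min/week activity endpoint, and sleep has no entry limit; adjust both threshold models for phase 1 device values

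*Protocol article*

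**What the plan says.** Four parts of the protocol article bear on this.

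- **Participants.** Exclusions rest on self-report ("We will exclude people who report"). One of them is "physical exercise of ≥200 minutes per week at a moderate or vigorous intensity or ≥10 hours of walking per week", and the stated reason is "as this raises the possibility of ceiling effects on activity".
- **Proposed Analyses and Analytical Approach.** For the second aim, the outcomes are continuous time spent on each behavior and the likelihood of reaching "recommended levels of physical activity (≥150 minutes of moderate to vigorous physical activity/week) and sleep (>7 hours/night" hours. The question is whether "participants who receive the innovative JIT intervention were more likely to meet recommended levels of physical activity or sleep". The approach is that of the first aim: a group effect and a group-by-time interaction in mixed models. Time is described as running across the intervention period. Phase 1 status is not mentioned for the threshold outcomes.
- **Objective Physical Activity.** Device stepping time is split into "light physical activity or moderate to vigorous physical activity using the 100 steps per minute cut point". No minimum bout length is stated.
- **Eligibility for Phase 2.** Survey compliance and valid nights are checked before entry, but "the physical activity data will not be assessed for completeness as it requires considerable time to download and review". No activity level or sleep duration criterion is applied.

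**The concern.** The exclusion exists to leave room for improvement in activity, yet for the binary endpoint its limit is set 50 minutes per week too high to guarantee that room. Someone who reports between 150 and 199 minutes of exercise may enter and may already be at the guideline level. The sleep endpoint has no entry limit at all, although no ceiling rationale is claimed for sleep.

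If a sizeable share of entrants is above a threshold before randomization, two things follow. The whole-sample difference understates the effect among people who could cross the line upwards. And much of the outcome's variance is stable between-person difference, which phase 1 data could remove but the stated group comparison leaves in the error. A null result on these endpoints would then be hard to read: it could mean an ineffective intervention or an insensitive contrast.

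**Working it through.** **Inputs from the article.** Endpoint 150 min/week; exclusion from 200 min/week of exercise or 10 h (600 min)/week of walking; cut point 100 steps/min; 210 participants randomized 2:1, and 210 × 2/3 = 140 JIT, 210 × 1/3 = 70 control, as stated under Sample Size. The target of 210 cannot be reproduced, because no alpha, power or effect size is given.

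**Overlap of the limits.** 200 − 150 = 50 min/week of reported exercise lies above the endpoint and still within eligibility. A person walking just under 600 min/week would need 150/600 = 25% of it at the cut point, about 150/7 = 21 min/day, to meet the endpoint.

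**Assumptions (not in the article).** A share *s* of each arm is above the line in phase 1. Among the rest, 20% of controls and 40% of JIT participants reach it. Two-sided alpha is 0.05, with one binary outcome per person. Those already above first stay above.

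**Unadjusted whole-sample comparison.** Control rate c = *s* + (1 − *s*) × 0.20; JIT rate t = *s* + (1 − *s*) × 0.40; difference = (1 − *s*) × 0.20. SE = √[c(1 − c)/70 + t(1 − t)/140]. Power uses the pooled variance under the null and this SE under the alternative.

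**Comparison stratified by phase 1 status, still in everyone.** If those above stay above, their stratum contributes zero difference and zero variance. The estimate is unchanged at (1 − *s*) × 0.20, and its SE is (1 − *s*) × √[0.16/(70(1 − *s*)) + 0.24/(140(1 − *s*))].

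| *s* | c vs t | Difference | Unadjusted SE | Unadjusted power | Stratified SE | Difference/SE, unadjusted → stratified |
|---|---|---|---|---|---|---|
| 0 | 20% vs 40% | 20 points | 6.3 | 84.7% | 6.3 | 3.16 → 3.16 |
| 20% | 36% vs 52% | 16 points | 7.1 | 59.4% | 5.7 | 2.25 → 2.83 |
| 40% | 52% vs 64% | 12 points | 7.2 | 38.8% | 4.9 | 1.66 → 2.45 |

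**Analysis restricted to those below the line.** The difference stays at 20 points with 70(1 − *s*) and 140(1 − *s*) people; power is 75.5% at *s* = 20% and 62.2% at *s* = 40%. Its difference/SE ratio equals the stratified one, since both numerator and SE are scaled by (1 − *s*). Under this assumption, restriction gains nothing over adjustment in the full sample.

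**Less extreme case.** If only 80% of those above stay above, equally in both arms, the stratum adds variance *s*² × 0.8 × 0.2 × [1/(70*s*) + 1/(140*s*)]. The ratio then moves from 2.29 to 2.57 at *s* = 20% and from 1.65 to 1.95 at *s* = 40%. The gain is smaller but still there.

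**Other starting rates.** With 10% versus 30% among the rest, unadjusted power falls from 93.2% (*s* = 0) to 37.6% (*s* = 40%); with 30% versus 50%, from 79.8% to 41.1%.

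**The case against.** The strongest reply is that nothing here is contradictory. The exclusion is meant to limit ceiling effects; it does not promise that every entrant is below the guideline. Asking who is more likely to meet recommended levels in the whole sample is a legitimate question, and restricting to people below the line asks a different one. An article need not list covariates, and an analysis plan that is not shown may already adjust. The same aim also tests the continuous outcome ("we will test these relationships using continuous outcome (ie, the amount of time spent on these health behaviors"), which the 150-minute cut does not affect.

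Most of this stands. It rules out making the baseline-defined subset the main estimate, and it keeps the point modest. It does not remove the overlap of the two limits, which are both fixed in the article, or the advantage of adjustment over the group comparison as described.

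Three stronger readings should be resisted.

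- A reader might infer that people above the line cannot contribute. They can fall below it, and preventing that is a treatment effect. Sleep is judged per night, so one person can cross 7 hours in either direction from night to night.
- A reader might infer that a chance imbalance in baseline achievers would pass for a treatment effect. Under randomization it is noise already reflected in the standard error, not bias.
- A reader might infer that everyone reporting 150 to 199 minutes is already a success. Entry uses self-report and the endpoint uses device stepping time. Exercise that is not stepping need not count, and the article gives no cadence figures for walkers.

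**Conclusion.** The point holds as a matter of sensitivity and interpretation, not validity. The activity entry limit lies above the activity endpoint and sleep has no entry limit, so some participants may already be above either threshold before randomization. The effect among those with room to improve is diluted by the factor (1 − *s*), and *s* is not given. The power figures are therefore illustrations resting on assumed shares, assumed rates and a single binary outcome per person, not on the repeated-measures model planned. They were worked for a weekly activity outcome; the loss for nightly sleep was not quantified. The endpoints concerned are companion analyses within the secondary aim. Because the phase 1 device data are collected before randomization, an easy improvement is available.

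**What to change.** Keep the intent-to-treat comparison of all randomized participants as the main estimate for both threshold outcomes. Adjust each model for the matching phase 1 device value: weekly minutes of moderate to vigorous activity for the activity threshold, mean total sleep time for the sleep threshold. Impute missing phase 1 values, since activity data are not checked at entry. Prespecify, as supporting only, the effect among participants below the threshold in phase 1, and report how many are above it in each arm.

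The cost is analysis wording and some imputation of baselines; no new data are needed. The supporting analysis has fewer people and rests on a single week of classification, which is why it should not replace the main estimate. The article reports that analyses have not begun, so on that account this can still be fixed in advance. If the full analysis plan already adjusts in this way, a sentence saying so is enough.
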